### Plans to promote participant retention and complete follow-up {18b}

For participants who withdraw consent, already collected data will be used for analyses, and if feasible and the participant agrees, the usual follow-up assessments will be conducted for data capture.

### Data management {19}

The data entry, coding, security, and storage procedures, including any related processes to promote data quality, will be performed according to the SOPs and the data management and validation plan provided by the sponsor and under the supervision of the designated clinical data manager of the sponsor.

### Confidentiality {27}

Only the study nurses and designated investigator site staff will enter the data required by the protocol into the system. Direct access to source documents will be permitted for purposes of monitoring, audits, and inspections.

### Plans for collection, laboratory evaluation, and storage of biological specimens for genetic or molecular analysis in this trial/future use {33}

This trial does not involve the collecting, laboratory evaluation or storage of biological specimens for genetic or molecular analysis.

Statistical methods

### Statistical methods for primary and secondary outcomes {20a}

#### Primary analysis

Baseline characteristics of the study participants will be summarized according to numbers and percentages for qualitative variables, means, and standard deviations for quantitative variables with normal distributions and medians and 25th–75th percentiles for quantitative variables with nonnormal distributions. Differences in the change in the primary outcome from baseline to the 6-month follow-up between the intervention and control group participants will be compared by linear regression analyses corrected for relevant confounders and baseline values. The same analysis will be used for continuous secondary outcomes. The primary analysis will be done with a one-sided nonpaired *t* test comparing the two groups with each other at the final visit at the end of the follow-up period.

For the main analyses, we will compare the control group with the intervention group using an intention-to-treat approach. This study is designed as a superiority study.

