**Methods:**

This is the protocol for a randomized, controlled, open-label, multicentered trial that will be carried out at inpatient PR hospital centers in Germany and Switzerland. The interventions will involve the use of the KAIA COPD app program (Arm 1) or an active comparator, i.e., usual care (Arm 2). Patients completing an in-hospital PR program and consenting to participate in the study will be screened with the inclusion and exclusion criteria and enrolled in the study. After fulfilling the screening requirements, the patients will be randomized into one of the two arms with parallel group assignment in a 1:1 ratio. The training program will be delivered to the participants grouped in Arm 1 via the KAIA COPD app and to participants grouped in Arm 2 via the regular recommendations or standard of care by the PI. In total, 104 participants will be included in the trial. The treatment period will last for 24 weeks. Electronic versions of questionnaires will be used to collect patient-reported assessments remotely. The primary outcome measure is the change in physical activity of the intervention group in comparison to the control group, measured over 1 week as the mean steps per day with a Polar A 370 activity tracker, from baseline (end of PR) to the 6-month follow-up. The secondary outcome measures are functional exercise capacity, health status, sleep quality, exacerbation rate, and depression and anxiety symptoms assessed at several intervals.

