### Sample size {14}

In total, 104 participants are expected to be recruited, 52 for the intervention group and 52 for the control group each. The sample size calculation is based on the primary outcome, the difference between groups in the average steps per day within 1 week at the 6-month follow-up. As this study had no pilot study, there are no further statistical sample size considerations. The well-established minimally important difference in steps per day after pulmonary rehabilitation lies between 600 and 1100 steps as measured with an activity tracker during an intervention. Assuming a standard deviation of the outcome variable of 2500 steps/day, an expected effect size of 2000 steps/day can be assumed for programs combining physical activity counseling with PR to increase activity, according to current meta-analyses. To achieve 80% power and a significance level of 5% (one-sided), a sample size of 26 patients in each group is required, which results in a total sample size of 104, assuming a drop-out rate of 50%. The sample calculation is based on a one-tailed nonpaired *t* test comparing the two groups with each other at the final visit at the end of the follow-up period.

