### Implementation {16c}

Randomization will be performed on the patient level with a 1:1 ratio using block randomization with varying block sizes, stratified per study center. Once the random number is delivered to the study site, it is the duty of the site personal to implement the procedures as specified in the protocol.

The study nurse will carry out a short training program (20 min) to demonstrate the use of the wearable and mobile device platform (smartphone) for both groups. Additionally, the following steps will be taken to explain the group assignment to the subjects.

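### The named primary test, an unadjusted final-visit t test, does not match the change outcome in the abstract, stands beside an unlabelled adjusted regression, and leaves out baseline steps and centre

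*Protocol article*

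**What the plan says.** All references are to the protocol article.

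- **Abstract, Methods.** "The primary outcome measure is the change in physical activity of the intervention group in comparison to the control group", from baseline (end of rehabilitation) to 6 months. The outcome is a change.
- **Sample size {14}.** The calculation rests on "the difference between groups in the average steps per day within 1 week at the 6-month follow-up", analysed by a one-tailed unpaired t test. The outcome is the final value.
- **Primary analysis, under {20a}, first statement.** The arms' changes in steps over the 6 months "will be compared by linear regression analyses corrected for relevant confounders and baseline values". The outcome is a change and the analysis is adjusted. The next sentence extends this analysis to the continuous secondary outcomes.
- **Primary analysis, second statement.** "The primary analysis will be done with a one-sided nonpaired"; the test in question is a t test of the two arms at the last visit. The outcome is the final value and the analysis is unadjusted.
- **Implementation {16c}.** Allocation is made "using block randomization with varying block sizes, stratified per study center". Neither analysis names centre.

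**The concern.** One heading holds two analyses of steps per day that differ in outcome (change or final value), in adjustment (baseline and confounders, or nothing) and possibly in result. The t test is called primary, but it does not analyse the outcome that the abstract declares. The regression does, yet it carries no label as primary, secondary or sensitivity.

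Two things are at stake. First, if the two results fall on opposite sides of the significance threshold, the article gives wording that supports reporting either one as the planned result. Second, the named test uses neither baseline steps, which are already collected and probably predict steps at 6 months, nor the factor that stratified the randomisation. With small arms, a chance difference in baseline activity goes straight into the estimate. The missing-data rule makes this sharper. Missing final values are replaced by baseline or last known values, and the sample size allows for 50% drop-out, so many of the 'final' values may in fact be early ones.

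**Working it through.** **Inputs from Sample size {14}.** Difference 2000 steps/day; SD 2500; one-sided 5%; 80% power; 26 evaluable per arm; 50% drop-out; minimally important difference 600 to 1100 steps.

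**Assumed input.** The correlation r between baseline and 6-month steps is not given. I use 0.4 to 0.7.

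**1. The plan's own figure.** For an unpaired t test with n per arm, the noncentrality is δ / (SD × √(2/n)) with 2n − 2 degrees of freedom. At one-sided 5%, 80% power needs 21 per arm (20 by the normal approximation), not 26. A two-sided 5% test needs 26. That mismatch is a separate point. The drop-out step is right: 26 / (1 − 0.5) = 52 per arm, 104 in total. The calculations below keep the stated 26 per arm and one-sided 5%.

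**2. Power of the named t test.** The standard error is 2500 × √(2/26) = 693.
- 2000 steps: noncentrality 2000/693 = 2.88, power 88.5%.
- 1100 steps: noncentrality 1100/693 = 1.59, power 46.8%.

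**3. Power after baseline adjustment.** Residual SD = 2500 × √(1 − r²). The one degree of freedom spent on baseline is ignored; its effect is below 0.1 percentage point.

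| r | Residual SD | Power, 2000 steps | Power, 1100 steps |
|---|---|---|---|
| 0 (t test) | 2500 | 88.5% | 46.8% |
| 0.4 | 2291 | 92.8% | 52.5% |
| 0.5 | 2165 | 95.0% | 56.4% |
| 0.7 | 1785 | 99.0% | 70.8% |

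Residual variance falls by r², that is by 16% to 49%. The gain from adding centre is not quantified, because the article gives nothing on differences between centres.

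**4. False-positive rate if either analysis may count.** Simulation under no effect, 26 per arm, each test at one-sided 5%, success if the t test or the baseline-adjusted model is significant:
- r = 0.4: about 6.5%
- r = 0.5: about 7.1%
- r = 0.7: about 8%

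Each test alone holds 5%. The excess comes only from having two candidates. A free choice of confounders is not included and could add to it.

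**5. Why one model settles the outcome question.** Let Y be 6-month steps, X baseline steps and Z the arm. If Y = a + τZ + bX + error, then Y − X = a + τZ + (b − 1)X + error. The treatment effect τ and its standard error are identical. Once baseline is a covariate, change and final value give the same answer, so the conflict between the abstract and the sample size section no longer affects the result.

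**The case against.** - **The t test is named as primary.** This stands. The Primary analysis section says so, and the sample size section uses the same test at the same visit. A reader might infer that the primary analysis is wholly undeclared; the article does not support that. The 6.5–8% figure therefore applies only if the sponsor treats the regression as an equal candidate. The deviations section requires departures to be reported to the ethics committee beforehand and justified, and statisticians or data managers are to be blinded. These safeguards lower the risk. They do not say what the regression is for, or why the named test leaves the abstract's outcome unanalysed.
- **The t test is valid.** This also stands. A reader might infer that leaving out baseline or the stratum biases the result or inflates the error rate. Under randomisation it does not, and omitting a stratification factor usually makes the test conservative. The loss is in precision and in protection against chance imbalance.
- **The confounder list belongs to the statistical analysis plan.** This is fair: its absence from an article is no fault in itself. It matters here only because the unlabelled regression could be taken for the primary model.
- **The power figures are conditional.** They are. They take SD 2500 as the SD of final values and 26 completers per arm, whereas the intention-to-treat set with carried-forward values could reach 52 per arm. A reader might also infer that the change outcome is badly underpowered. On the same SD assumption, an unadjusted test of change has SD 2500 × √(2(1 − r)) and power 77.6% at r = 0.3, 88.5% at 0.5 and 97.9% at 0.7. It loses to the final-value t test only when r is below 0.5.

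**Conclusion.** The concern holds in a limited form. The article names a primary test, but that test does not match the change outcome in its abstract, and an adjusted regression of unstated role stands beside it. This is a contradiction in the text, and an analysis plan could not follow both statements.

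The omission of baseline steps and centre is a matter of efficiency and chance imbalance. For r between 0.4 and 0.7, baseline adjustment is worth about 4 to 10 percentage points of power at 2000 steps (88.5% to 92.8–99.0%) and 6 to 24 points at 1100 steps (46.8% to 52.5–70.8%). Even with adjustment, power at 1100 steps stays below 80% over that range. The false-positive rate of about 6.5–8% is conditional on either analysis being claimable as primary. All these figures rest on the assumed r, SD 2500 for final values, and 26 per arm at the stated one-sided 5%. Whether the test should be one-sided or two-sided is a separate question and does not affect this conclusion.

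**What to change.** Name one primary analysis: a linear model of mean steps per day at 6 months, with treatment arm, baseline steps and study centre, and no other covariates. State that the treatment effect is the same if change is modelled. Then:

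- align the outcome wording in the abstract, Sample size {14} and Primary analysis to this model;
- take the open-ended confounder adjustment out of the primary model; any further adjusted model is labelled as secondary or sensitivity, with its covariates listed in advance;
- keep the unpaired t test as a labelled sensitivity analysis.

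No new data are needed: baseline steps and centre are already recorded. The cost is procedural. Recruitment began in August 2019, so replacing the primary test calls for a protocol amendment, submission to the ethics committees and an entry in the trial register, all completed before analysis.

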#### Per-protocol analysis

As a sensitivity analysis, we will additionally conduct a per-protocol analysis, where we will also compare the control group with the intervention group but where we will only retain those participants in the intervention group who adhered to the intervention for the analyses.

We define adherence to the protocol (in terms of exercise training) as conducting the exercise training sessions for at least 70% of the weeks the patients are able to train (i.e., weeks when patients suffered from exacerbations or other health conditions that prevent them from training will not be considered; as discussed with the coach), for at least 4 times a week, during the 6 months of the intervention (see the following definitions):
Definition of a fulfilled individualized training session per day (according to the protocol: 3 different exercises per day are scheduled): completion of at least 2 different exercises per dayDefinition of a fulfilled week of training (rate of training sessions according to the protocol: 4 per week): completion of at least 4 out of the planned 7 individualized training sessions per week on average.

We will adjust the per-protocol analyses with prognostic factors for the primary outcome steps per day, lung function (FEV1), exercise capacity and exacerbation events, for adherence to conduction of the exercises (self-efficacy to conduct the exercises, exercise capacity, dyspnea, and acute worsening of health state [exacerbations and other]) and for whether the patients conducted other exercise strength training.

Concerning the control group, we will collect as much information as possible, especially with respect to the type and frequency of self-organized exercise training. This will also be included in the per-protocol analysis.

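### The per-protocol analysis selects adherers in the app arm only and adjusts for post-randomisation events, so its agreement with intention-to-treat would not show robustness

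*Protocol article*

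**What the plan says.** All of the following is in the protocol article, section Per-protocol analysis, unless another section is named.

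- Role: "As a sensitivity analysis, we will additionally conduct a per-protocol analysis".
- App arm: "we will only retain those participants in the intervention group who adhered to the intervention for the analyses".
- Control arm: no adherence filter is stated. The text says "Concerning the control group, we will collect as much information as possible, especially with respect to the type and frequency of self-organized exercise training", and that this information will enter the analysis, without saying how.
- Adherence: "conducting the exercise training sessions for at least 70% of the weeks the patients are able to train", at 4 or more sessions a week over the 6 months. Sick weeks leave the denominator: "weeks when patients suffered from exacerbations or other health conditions that prevent them from training will not be considered". This is settled in discussion with the coach. A fulfilled week is then defined as "completion of at least 4 out of the planned 7 individualized training sessions per week on average".
- Covariates: "lung function (FEV1), exercise capacity and exacerbation events"; predictors of adherence (self-efficacy, exercise capacity, dyspnoea and "acute worsening of health state [exacerbations and other"]); and whether patients did other strength training.

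The Primary analysis section makes intention-to-treat the main comparison, for superiority. The Abstract lists exacerbation rate among the secondary outcomes.

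**The concern.** A sensitivity analysis should address the same question as the main analysis under different assumptions, so that agreement is reassuring. This one addresses a different question in a non-randomised comparison. Patients who train on at least 4 days a week in most of the weeks they are able to are likely to be healthier, more motivated and more active than the average patient. They are set against controls to whom no such filter is applied. Adherence is also close in kind to the outcome: the app that delivers the training also sets weekly step goals and sends reminders (section Exercise concept).

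The adjustment is a separate difficulty. Exacerbations, acute worsening and other training happen during follow-up and may be consequences of allocation. Holding them fixed can remove part of a real effect or create a spurious one.

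At stake is interpretation. A neutral intention-to-treat result could stand beside a favourable per-protocol result that reflects selection, or two agreeing results could be read as mutual confirmation that they do not provide.

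**Working it through.** The plan attaches no figure to this analysis, so there is none to reproduce. The question is how large the selection bias could be.

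**Inputs from the protocol** (section Sample size; allocation also in Trial design): SD 2500 steps/day; 52 patients per arm; one-sided 5% test; minimally important difference 600 to 1100 steps/day.

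**Assumptions, not in the protocol:** share of the app arm that adheres, p = 50%, 70% or 90%; correlation r between tendency to adhere and 6-month steps, 0.1 to 0.5; no app effect; all 52 controls kept; no covariate adjustment.

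**Step 1, selection bias without adjustment.** If the most adherent share p is kept, bias = r × SD × φ(c)/p, where c is the standard normal cut-off exceeded by a share p. For p = 0.5, c = 0 and φ(c) = 0.399, so at r = 0.3 the bias is 0.3 × 2500 × 0.399/0.5 = 598 steps/day.

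**Step 2, false-positive rate.** This is the power of the one-sided t test at that bias, with noncentrality = bias / (SD × √(1/n₁ + 1/n₂)). For 26 against 52: 598 / (2500 × √(1/26 + 1/52)) = 598/600 ≈ 1.0, giving about 26%. The SD among adherers is taken as 2500, a slight simplification.

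| App arm adherent (patients) | r = 0.1 | r = 0.2 | r = 0.3 | r = 0.5 |
|---|---|---|---|---|
| 50% (26) | 199 (9%) | 399 (16%) | 598 (26%) | 997 (50%) |
| 70% (36) | 124 (8%) | 248 (12%) | 373 (17%) | 621 (31%) |
| 90% (47) | 49 (6%) | 97 (7%) | 146 (9%) | 244 (12%) |

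Entries are steps/day, with the false-positive rate in brackets. At r = 0 the bias is zero and the rate is 5%.

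**Step 3, what adjustment does to the selection bias.** A simulation with 1,000,000 patients per scenario, 50% adherent and no app effect used assumed relations. A measured baseline factor and an unmeasured health factor drive adherence and exacerbations, the baseline factor also drives steps, and the unmeasured factor does so to a degree that was varied from none upwards. Exacerbations lower both adherence and steps.

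- Intention-to-treat difference: about 0.
- Per-protocol, unadjusted: 614 to 888 steps/day.
- Adjusted for the baseline factor: 65 to 359.
- Adjusted for exacerbations as well: 2 to 257.
- Adjusted for the unmeasured factor too: about 0.

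Adjustment helps, but it removes the bias reliably only when every common cause of adherence and steps is in the model.

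**Step 4, what adjusting for a post-randomisation event does on its own.** The same model was run with an app that lowers exacerbations, and with all randomised patients kept. The total effect was 104 to 111 steps/day. Adjusting for exacerbations moved the estimate to between -79 and -3, that is, against the app. The sign is not fixed. For example, if app users gave up other strength training that raises steps, holding that training constant would credit the app with more than its total effect.

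**Step 5, the weekly rule.** A patient with 7 sessions in 12 weeks and 1 in the other 12 averages (84 + 12)/24 = 4 per week but fulfils only 12/24 = 50% of weeks. Applied week by week, the 70% rule classes this patient as non-adherent. Only a literal reading of the averaging words would say otherwise.

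**The case against.** The strongest reply is that the authors foresaw the selection. They adjust for prognostic factors and for predictors of adherence, which is what one would do to reduce it. This stands in part. The table does not describe the planned analysis, and the residual bias after adjustment is unknown. The protocol gives neither the adherent share nor the correlation, and with 90% adherent the bias is modest.

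Several stronger readings are tempting and should be resisted.

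- *The analysis is certainly biased towards the app.* The direction is likely, but it depends on a correlation that the protocol does not give.
- *The adjustment adds to a bias in favour of the app.* Step 4 shows that it can work the other way.
- *All the covariates are post-randomisation.* No timing is given for FEV1, exercise capacity, self-efficacy or dyspnoea; these may be baseline values.
- *Every control is kept.* This is inferred from the absence of a stated filter; how control self-training data enter is left open.
- *The adherence rule contradicts itself.* The definitions are nested: session, then week, then patient. The averaging words sit inside the definition of a week and are loose wording, not a rival patient-level rule.
- *A favourable per-protocol result could override a neutral main result.* Nothing in the protocol provides for that.

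The adjustment argument does not rescue the label. Even a well-adjusted comparison of adherers with controls addresses a different question from intention-to-treat and relies on there being no unmeasured common cause.

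**Conclusion.** The point holds in limited form. The plan fixes a one-arm selection on behaviour after randomisation and adds covariates that also arise after randomisation, one of which is a secondary outcome. The selection breaks the randomised comparison and probably favours the app. Without adjustment and with no app effect, it could reach the protocol's own minimally important difference (600 to 1100 steps/day) in the upper part of the assumed range: at correlations of about 0.3 and above with 50% adherent, and about 0.5 with 70% adherent. At 90% it stays well below. The planned adjustment would reduce these figures by an amount that cannot be derived from the protocol, while the post-randomisation covariates make the result hard to interpret in either direction.

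The analysis can be reported, but not as evidence that the intention-to-treat result is robust. Because intention-to-treat remains the main analysis, this is something that should be corrected and not a flaw in the primary result.

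**What to change.** 1. Stop calling it a sensitivity analysis. Label it supplementary and state that selection in one arm may favour the app.
2. Remove exacerbation events, acute worsening and other strength training from the model. Use baseline values only: steps, FEV1, exercise capacity, self-efficacy, dyspnoea and centre.
3. For an effect under adherence, add an estimate that keeps all randomised patients in both arms, for example a complier-average causal effect with randomisation as instrument, also reported as supplementary.
4. Delete the averaging words from the definition of a fulfilled week, so that the 70% rule is applied week by week.

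The cost is wording and modest programming, with two statistical prices. First, removing exacerbations may leave more selection bias in the one-arm comparison (65 to 359 instead of 2 to 257 steps/day in Step 3), which is why the warning in item 1 is needed. Second, the complier-average estimate divides the intention-to-treat effect by p, so at 50% adherence its interval is roughly twice as wide. It also assumes that non-adherers gain nothing from allocation. That is doubtful here, because app-arm patients below the threshold still have step goals and reminders (section Exercise concept) and are telephoned when they train too little (section Intervention description). If adherers gain e and non-adherers gain b, the estimate is e + b(1 - p)/p, which is e + b at p = 0.5. It may therefore overstate the effect, and the report should say so.
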